This trial aims to address the gap by delivering and evaluating a comprehensive, multidimensional geriatric assessment with care coordination in a community setting. The Older Persons ENablement And Rehabilitation for Complex Health conditions (OPEN ARCH) model of care evolved from an initial study that explored patient well-being post hospitalisation [10]. That completed study examined patients’ transition back to primary healthcare and their access to allied health and social support services within the community [10]. This current OPEN ARCH intervention builds on previous research [4, 10] and extends the service to preventative service delivered in a community setting; it creates a direct path from a general practitioner (GP) to a community-based geriatrician-led Healthy Ageing Clinic for comprehensive interdisciplinary assessment and care planning. The OPEN ARCH intervention will facilitate timely access to primary healthcare, including allied health services and social supports within the community. It is envisaged that the OPEN ARCH intervention will delay health decline by increasing individual capacity, when supported by a team of community healthcare professionals, who monitor and manage the community-dwelling complex older patients within the community. Such coordinated care support is expected to reduce the likelihood of the aforementioned cascade of events that leads to hospitalisation, and eventual loss of independence following hospital discharge.

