## Objectives

The objective of the study is to assess the acceptability of the OPEN ARCH intervention and its impact on the health and quality of life outcomes, health and social services utilisation of older people with multiple chronic conditions and emerging complex care needs. An economic evaluation will determine whether OPEN ARCH is cost-effective when compared to the standard care. In particular, this study will address the following research questions:Does the OPEN ARCH intervention result in reduced hospital care demand as measured by Emergency Department (ED) presentations, hospital admissions and in-patient bed days?Does the OPEN ARCH intervention result in reduced functional decline and dependency, and enable patients to live in the community for longer?Does the OPEN ARCH intervention result in an improved quality of life for participants?Is the OPEN ARCH intervention considered by participants to be an acceptable model of care?Is the OPEN ARCH intervention a cost-effective means to achieving better health and quality of life outcomes for at-risk older persons when compared to standard care?

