### Participants’ eligibility criteria

#### Sample size

Bird et al. [5] reported suitable comparative outcomes from a similar study. Following the stepped wedge study design with repeated cross-sectional samples recommendations of Barker et al. [16] and the applied parameters of Bird et al. [5], at least two clusters will be randomised at each step to ensure the nominal 5% significance level. Bird et al. [5] reached statistical significance using ANOVAs and *t* tests over three measures: ED presentations, hospital admissions and bed days. Pre verses post improvement for these three measures was 10%, 25% and 18% respectively. Following consultations with clinical and statistical experts, a conservative effect size across ED and in-patient services utilisation of 9%, a 10% intra-cluster correlation and between-cluster variations of 30% were assumed for the current study. The intervention will be staged in steps, each with at least two clusters/GPs, totalling a minimum of 10 GPs (clusters), who will each recruit 10–12 participants to the study. Allowing for 25% censoring, a sample size of 120 participants will be required, which will provide 80% power to detect a 9% difference (effect size) in service utilisation with statistical significance at the 5% level. The study design incorporates the effects of ‘time’. Sample size calculations were performed using the stepped wedge command in STATA 15 [18].

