### Intervention and comparison

The OPEN ARCH intervention has two components: fast-track specialist geriatric assessment via a community-based referral to a geriatrician in local GP practices; and an enablement service offering coordination and implementation of health and social care services customised to patient need in the community. The OPEN ARCH intervention will be delivered within primary healthcare. Patients who are deemed eligible by GP screening evaluation and meet inclusion criteria will be invited to provide informed consent. 

During the first interview and assessment, the geriatrician will provide an in-depth, standardised comprehensive geriatric assessment (CGA), a multi-dimensional, interdisciplinary process used to quantify an older individual’s medical, psychosocial and functional capabilities, including diagnosis, identification of problems, goal-setting and forming an individualised comprehensive management plan for holistic treatment, rehabilitation, support and follow up [19]. Alternatively, if the participant is unable to attend the assessment at the practice, a geriatrician will offer a home visit. The type and number of referrals to primary allied healthcare professionals and community support services will be determined by individual clinical needs and delivered in the community (GP, allied health practice or community health centre) or at home. Examples of allied health services that will be offered include: occupational therapy, physiotherapy, dietetics and social work. Community social support services such as personal care assistance, meals and domestic assistance will be arranged through My Aged Care and community health providers.

Upon completion of the initial interview and assessment, the geriatrician and enablement officer will meet with GP via face-to-face case conferencing, to complete the CGA with recommendations. The following Medicare Benefits Schedule (MBS) items will be available to GPs to claim: Item Numbers 735, 739 and 743 [20].

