### Clinical outcomes

#### Primary outcome measures

The primary outcome is service utilisation including: Emergency Department (ED) presentations, hospital admissions, in-patient bed days, allied health and support services utilisation. Hospital and ED data will be extracted from Queensland Health routinely collected computerised patient activity records. The number and type of appointments with the primary care physician and community-based allied health, nursing and social support services will be collated from medical clinic records kept by the engagement officers. A purpose-built data input form will be used to collate health and support service usage.

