### Statistical methods to assess intervention effect

The primary outcome measures, including Emergency Department (ED) presentations, hospital admissions, in-patient bed days, allied health and support services utilisation, will be analysed as panels between each cross-sectional time point of the stepped wedge design, comparing primary outcomes within and between clusters. Each cross-section will include participants undertaking the intervention as well as those receiving standard care (pre-intervention component). In addition to assessing intervention effects, the stepped wedge design can also model the effects of time to determine whether the time of intervention (intervening early versus intervening late) impacts the effectiveness of the intervention. Secondary outcome measures, including functional status, ISAR and QoL measures, will be compared for the pre versus post intervention periods, for each participant, and thus the participants will act as their own control. Participants’ experience of the OPEN ARCH intervention as measured by the Likert scale responses will be analysed using descriptive statistics.

Within-cluster and between-cluster variance, treatment outcomes for intervention versus pre-intervention, across time, will be examined by applying a generalised linear mixed model (GLMM), as recommended for small cluster designed stepped wedge studies [16]. GLMM models can be adjusted for unequal numbers within clusters and cope with non-parametric data distributions. Within the GLMM, primary and secondary outcomes will be assessed against time and intervention status, represented as fixed effects, while study clusters and clients will be represented in the model as random effects [16]. Secondary outcome analyses will include *t* tests (for continuous data), chi-square tests (for proportions) and GLMMs where applicable, to control for demographic differences. All statistical tests will be two-sided and performed using a 5% significance level with no adjustment for multiplicity. Data analysis will be performed using STATA version 15 [18].

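### Four or five service-use measures are all primary, each tested at 5% with adjustment ruled out, although the research question and assumed effect concern hospital use only and community-service use would be expected to rise

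*Protocol article*

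**What the plan says.** The section on primary outcome measures states: "The primary outcome is service utilisation including: Emergency Department (ED) presentations, hospital admissions, in-patient bed days, allied health and support services utilisation". That is five measures, or four if allied health and support services are read as one. The abstract gives a similar list.

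The section on statistical methods treats them as several outcomes. They "will be analysed as panels between each cross-sectional time point of the stepped wedge design, comparing primary outcomes within and between clusters". It gives no composite, weighting, lead measure, testing order or rule that all must succeed. On error control it is explicit: "All statistical tests will be two-sided and performed using a 5% significance level with no adjustment for multiplicity".

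Two other places point to a narrower target. The first research question under Objectives asks about "reduced hospital care demand as measured by Emergency Department (ED) presentations, hospital admissions and in-patient bed days", and no research question sets a direction for allied health or support service use. Under Sample size, "a conservative effect size across ED and in-patient services utilisation of 9%, a 10% intra-cluster correlation and between-cluster variations of 30% were assumed". The power sentence that follows, however, claims 80% power for a 9% difference in service utilisation without that restriction.

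On the community services, the Background says: "The OPEN ARCH intervention will facilitate timely access to primary healthcare, including allied health services and social supports within the community". The section on intervention and comparison adds: "The type and number of referrals to primary allied healthcare professionals and community support services will be determined by individual clinical needs". It also has the enablement officer link participants with existing services.

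**The concern.** Two features combine.

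First, several outcomes carry the label primary, each is tested at the full 5%, and nothing says which result, or how many, would answer the primary question. If one significant result were enough, the error rate of the trial's main claim would exceed 5%.

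Second, the outcomes differ in kind. Fewer ED presentations, admissions or bed days would be a benefit. More allied health or support contacts would mainly show that participants were referred and linked as planned. As written, a significant rise in those contacts is a significant primary result, even if hospital use has not changed.

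The Discussion in the abstract says that the results will bear directly on wider implementation of the model. Readers therefore need to know which finding is the test of it.

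**Working it through.** **1. Which measures each part of the article covers**

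| Part of the article | ED, admissions, bed days | Allied health, support services |
|---|---|---|
| Primary outcome measures | yes | yes |
| First research question | yes, reduction | not mentioned |
| Assumed 9% effect | yes | no |
| Power sentence | service utilisation, unrestricted | service utilisation, unrestricted |
| What the intervention facilitates | no | yes |

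The comparative study cited under Sample size also supplies figures for the three hospital measures only: improvements of 10%, 25% and 18%. No effect is assumed for community services.

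**2. The plan's own figure**

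The sample size is consistent as a count: 10 GPs × 12 participants = 120, and 90 evaluable participants / (1 − 0.25) = 120. The 80% power cannot be reproduced, because no baseline rate or standard deviation is given. The steps below do not depend on it, except that step 4 takes 80% as the starting point.

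**3. Chance of at least one false positive over the three hospital measures**

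Inputs: k = 3 tests, two-sided alpha 0.05 each (statistical methods section), all three null hypotheses true, and success declared on any one. The last condition is an assumption; the article does not state it.

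- Independent tests: 1 − 0.95³ = 1 − 0.857 = 14.3%.
- Tests with a common correlation ρ: 1 − ∫ [Φ((1.96 − √ρ·x)/√(1 − ρ)) − Φ((−1.96 − √ρ·x)/√(1 − ρ))]³ φ(x) dx, integrated numerically.

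| Assumed ρ | False-positive chance, 3 tests |
|---|---|
| 0 | 14.3% |
| 0.5 | 12.5% |
| 0.7 | 10.9% |
| 0.9 | 8.4% |

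The article gives no correlations, so the range is about 8% to 14%. Independence is its upper end and is unlikely here, because bed days arise from admissions.

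For comparison, five independent tests give 1 − 0.95⁵ = 22.6%, and four give 1 − 0.95⁴ = 18.5%. These apply only if the intervention also leaves community-service use unchanged.

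**4. Power cost of adjusting over three measures**

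A design with exactly 80% power at two-sided 5% has a standardised effect of 1.960 + 0.842 = 2.802. Bonferroni over three measures, which is also Holm's first step, uses 0.05/3 = 0.0167, with critical value 2.394. Power is then Φ(2.802 − 2.394) = 65.8%. Restoring 80% would multiply the sample size by ((2.394 + 0.842)/2.802)² = 1.334, from 120 to about 160. A single primary outcome avoids this cost.

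**The case against.** The strongest reply is that the article nowhere says that one significant result means success. A condensed article may leave the success rule to the full protocol or analysis plan. If that rule were a single lead outcome, or that all measures must succeed, no adjustment would be needed and the multiplicity sentence would be compatible with it. Openly declared, outcome-by-outcome reporting is also a defensible style. This stands to the extent that the 8% to 14% is conditional on an any-one-wins reading. It does not remove the point: the article itself labels all the measures primary and itself rules out adjustment. Those are stated choices, not details left open.

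Three stronger readings are tempting, and the document does not support them.

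- A reader might quote 22.6% as the trial's error rate. That needs five true null hypotheses and independent tests. It conflicts with the expectation that community-service use really changes, since a true change cannot be a false positive.
- A reader might infer that a rise in community services would cancel a fall in hospital use. That needs a summed composite, and none is stated. With separate two-sided tests, opposite directions are not in themselves contradictory.
- A reader might call the rise in community-service use certain. Referrals depend on individual need, and no increase is stated as a hypothesis. The rise is a reasonable inference from what the intervention does, and no more.

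**Conclusion.** The point holds in this form. The set of primary outcomes is wider than the research question and the assumed effect. It includes measures of what the intervention delivers, and every measure is tested at 5% with adjustment excluded and no lead outcome named. A rise in referred services could therefore be reported as a primary result.

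For the hospital measures, the false-positive chance is about 8% to 14% instead of 5%. That rests on an any-one-wins reading, three true null hypotheses and assumed correlations from 0.9 down to 0. It would be wrong to conclude that the plan commits to an invalid decision rule: it states none. The stated sample size is neither confirmed nor refuted by this check.

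**What to change.** Before the final analysis:

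- Name one of ED presentations, admissions or bed days as the single primary outcome. Alpha stays at 5% and the sample size at 120.
- Make the other two hospital measures secondary. Make allied health and support service use secondary or process outcomes, with the expected direction (increase) stated.
- Amend the multiplicity sentence to match, and make the power sentence refer to the hospital outcome, as the 9% assumption already does.

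If all three hospital measures must stay primary, test them in a fixed order at 5%, where each later measure is tested only if the one before it succeeds. Holm is the other option, provided the plan acknowledges that power at its first step falls from 80% to about 66% per outcome.

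The preferred option costs only wording in the protocol, registration and analysis plan. The article reports the trial as 6 months post baseline in November 2018, with collection planned to 9 months, and says that participants, GPs, enablement officers and the project manager are not blinded. The change should therefore be dated and its timing relative to any look at outcome data reported.

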### Economic evaluation

The economic research question is whether the OPEN ARCH intervention is cost-effective in reducing hospital utilisation and enhancing health-related quality of life when compared to the standard care. The perspective for the evaluation model will be a healthcare provider in the Australian setting [27].

Costs of the intervention will be incurred during the CGA and management. The CGA and management costs include the average time with each participant of different personnel, such as a GP, community-embedded specialist in geriatric medicine and community-based care coordinator. Costs of consecutive ED presentations, hospital admissions and hospital length of stay will be included. The cost of the pre-intervention care will include healthcare services utilisation before the initial GP consultation and CGA. Trial initiation, patient accrual and pre-screening activities as well as research and evaluation costs will be recorded and reported separately [28, 29].

Resources will be measured on a patient-specific basis obtained from the purpose-built data input form collated by the project manager from routinely collected computerised patient activity records and medical clinic records, following informed consent processes. Utilisation of objective data is known to eliminate patient recall bias and reduce the amount of missing data [30]. The cost of the time will be derived from a log of time spent on direct patient care activities. A top-down approach will be used to value resource use for capital and operating costs. Healthcare resource use data will be valued using Australian Independent Hospital Pricing Authority standard costs [31] reported in 2018 AUS$.

QALYs will be generated using a multi-attribute utility instrument, the EuroQoL 5-Dimension (EQ-5D-5L) scale [24]. This standardised, five-item descriptive system and visual analogue scale measures mobility, self-care, pain, usual activities and anxiety, and contributes to a ‘utility’ score. The AQOL-8D [32] instrument will be used to generate alternative QALYs. The AQOL-8D consists of eight dimensions: physical, including independent living, senses and pain; and psycho-social, including mental health, happiness, self-worth, coping and relationships. Utility weights for the AQOL were generated using the time-trade-off technique and Australian population sample. Due to its robust psychometric properties, the AQOL is recommended for use in epidemiologic studies where health-related QoL and utility data are required from older populations [33]. The AQOL has been used in Australian community older persons and Indigenous Australians studies [25].

The time horizon of the economic analysis will incorporate the lifetime of the cohort, through extrapolation of quality-adjusted survival from the end of the study period. A discount rate of 5% per year will be applied to both costs and outcomes [34]. The difference in costs and QALYs, between the intervention and pre-intervention periods, will be combined into the incremental cost-effectiveness ratio (ICER) with valuations of the willingness to pay for a marginal QALY to estimate the net monetary benefits for a decision to adopt the intervention:$$ \mathrm{ICER}=\frac{{\mathrm{Cost}}_{\mathrm{Int}}-{\mathrm{Cost}}_{\mathrm{Pre}-\operatorname{int}}}{{\mathrm{QALY}}_{\mathrm{Int}}-{\mathrm{QALY}}_{\mathrm{Pre}-\operatorname{int}}}, $$where Cost_Int_(Cost_Pre − int_) and QALY_Int_ (QALY_Pre − int_) are the mean cost and QALYs gained in the intervention (pre-intervention) periods, respectively. The maximum willingness to pay for a QALY will be assumed to be AUS$64,000 for the Australian setting [35]. The Markov state transition process will be applied to model participants’ probability of being readmitted to hospital, staying in the community or dying [36]. Sensitivity analysis will be performed to test variations in key parameters including the study perspective, the choice of the comparator and specific cost impacts.

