**Methods/design:**

This multicentre randomised controlled trial uses a stepped wedge cluster design with repeated cross-sectional samples. General practitioners (GPs; *n* ≥ 10) will be randomised as ‘clusters’ at baseline using simple randomisation. Each GP cluster will recruit 10–12 participants. Data will be collected on each participant at 3-month intervals (− 3, 0, 3, 6 and 9 months). The primary outcome is health and social service utilisation as measured by Emergency Department presentations, hospital admissions, in-patient bed days, allied health and community support services. Secondary outcomes include functional status, quality of life and participants’ satisfaction. Cost-effectiveness of the intervention will be assessed as the change to cost outcomes, including the cost of implementing the intervention and subsequent use of services, and the change to health benefits represented by quality adjusted life years.

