## Discussion

The OPEN ARCH intervention is based on the geriatric evaluation and management (GEM) model of care. It builds on previous work that explored patient experiences of transitions from the GEM service to primary healthcare [4]. This successful study noted, upon conclusion, that further improvements to geriatric care could be made by offering early intervention and prevention through improved screening and comprehensive assessment in primary care [10].

Thus, this proposed OPEN ARCH study has been designed to address the deficit identified within the original hospital discharge model, through the provision of a community facing preventative care. By providing the care in the community, condition deterioration can be detected earlier and enable timely planning for permanent residential aged care placement, where needed, reducing the likelihood of unexpected hospital admissions from community-residing patients. Furthermore, with fewer hospitalisations, older people are likely to achieve better well-being outcomes if they remain living independently and well supported in the community [2].

The feasibility and sustainability of the OPEN ARCH intervention are ensured by the placement of the intervention within primary care settings and MBS funding available to GPs (Item Numbers 735, 739, 743); utilisation of case conferencing and shared medical records. Further, providing knowledge translation, education and support with system navigation skills to both GPs and practice nurses will ensure a long-term solution to issues related to system functioning and integration. This trial will determine the impact of the OPEN ARCH intervention on the health and quality of life outcomes, health and social services utilisation of older people who have multiple chronic conditions and emerging complex care needs. The trial will involve an economic evaluation to determine whether the model can be considered cost-effective when compared to the standard care.

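### The lifetime model has no residential-care state, no outcome covers time living in the community, and the two periods' cost scopes are described inconsistently

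*Protocol article*

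**What the plan says.** **Model states.** In the Economic evaluation section, the Markov process models each participant's "probability of being readmitted to hospital, staying in the community or dying", over the lifetime of the cohort. The Exclusion criteria keep out people already in residential aged care, so everyone enters from the community. The Background names permanent placement as a possible consequence of hospitalisation. The Discussion says that care in the community can "enable timely planning for permanent residential aged care placement, where needed, reducing the likelihood of unexpected hospital admissions".

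**Research question 2.** The Objectives ask whether OPEN ARCH leads to "reduced functional decline and dependency, and enable patients to live in the community for longer". The primary outcome is service use (ED, admissions, bed days, allied health and support services). The secondary outcomes are the Functional Independence Measure, ISAR, two quality-of-life instruments and a satisfaction questionnaire.

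**Cost scope.** For the intervention, "The CGA and management costs include the average time with each participant of different personnel", and "Costs of consecutive ED presentations, hospital admissions and hospital length of stay will be included". For the comparator, "The cost of the pre-intervention care will include healthcare services utilisation before the initial GP consultation and CGA". The abstract describes cost outcomes as "including the cost of implementing the intervention and subsequent use of services". The only price source named for resource use is a hospital pricing authority. The perspective is that of a healthcare provider.

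**The concern.** A participant who moves permanently into residential care is not in hospital, is not dead, and is no longer living in the community in the sense used by the Objectives and the Exclusion criteria. The model has no proper place for that person, yet the Discussion links planned placement to fewer unexpected admissions. With a lifetime horizon, whatever cost and utility such a person is given carries through every later cycle.

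The same event decides the second half of research question 2, and nothing in the outcome list captures it.

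The ICER numerator is intervention cost minus pre-intervention cost, so a difference in what is counted on the two sides enters it directly. The Intervention and comparison section makes allied health and support referrals a product of OPEN ARCH. If they were not costed after the intervention starts, care moved from hospital to community services would look like a saving.

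**Working it through.** The article gives no ICER, incremental cost, QALY gain or unit cost, so there is no figure of the plan to reproduce. The check sets the statements side by side and then shows how much the gaps could matter.

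**1. States against expected events**

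| Event | Where the article expects it | State in the model |
|---|---|---|
| Hospital readmission | Objectives, Primary outcome measures | yes |
| Living in the community | Objectives | yes |
| Death | Economic evaluation | yes |
| Permanent residential care | Background, Discussion; excluded at entry | none |

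**2. Research question 2 against outcomes**

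- Functional decline and dependency: Functional Independence Measure and ISAR.
- Living longer in the community: no outcome listed in either outcome section.

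**3. Cost categories named**

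| Category | Pre-intervention | After the intervention starts |
|---|---|---|
| ED, admissions, length of stay | within the general wording | named |
| GP, geriatrician and coordinator time for CGA and management | not applicable | named |
| Allied health, nursing, support services | health services within the general wording; support services unclear | not named in Economic evaluation; within the abstract's wording |

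**4. Size of a gap in community costs.** The only input from the article is the willingness to pay, AUS$64,000 per QALY. The QALY equivalent of an uncounted cost X per participant is X / 64,000:

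- 500 / 64,000 = 0.0078
- 1,000 / 64,000 = 0.0156
- 2,000 / 64,000 = 0.0312

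The effect on the decision compares ICER = dC / dQ with (dC + X) / dQ. Here dC (counted incremental cost), dQ (QALY gain) and X are assumptions:

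| dC (AUS$) | dQ | X (AUS$) | ICER without X | ICER with X | Crosses 64,000? |
|---|---|---|---|---|---|
| 1,000 | 0.02 | 500 | 50,000 | 75,000 | yes |
| 1,000 | 0.02 | 2,000 | 50,000 | 150,000 | yes |
| 1,000 | 0.05 | 500 | 20,000 | 30,000 | no |
| 1,000 | 0.05 | 2,000 | 20,000 | 60,000 | no |

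**5. Direction of the error from the missing state.** Assume residential care costs R = AUS$40,000 to 80,000 per year and OPEN ARCH changes time in residential care by d = -0.1 to +0.1 years per participant. The uncounted incremental cost is R × d:

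- 40,000 × (±0.1) = ±AUS$4,000
- 80,000 × (±0.1) = ±AUS$8,000

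If OPEN ARCH delays placement (d negative), leaving the state out hides a saving and counts against the intervention. If placement comes earlier (d positive), leaving it out favours the intervention.

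**The case against.** A reader might infer that community services are omitted from the costing. The text does not go that far. The list of hospital items is not exclusive, and the abstract's wording has no hospital limit. The Economic evaluation section also states that "Resources will be measured on a patient-specific basis obtained from the purpose-built data input form", and Primary outcome measures says this form holds support service use as well as health service use. The data will therefore exist. What stands is that the sections describe the cost scope differently and that no price source suited to community services is named.

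A reader might also infer that the ICER is tilted towards OPEN ARCH. For community costs that needs two conditions: the services rise, and they are left out. For residential care the sign is open, and the stated aim of longer community living would push the error the other way. The Discussion speaks of timely planning where needed, not of earlier placement.

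Nor is research question 2 wholly unmeasured, since its functional half has two instruments.

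The healthcare-provider perspective could properly leave some social support and residential-care costs out of the base case, and sensitivity analyses on perspective and specific cost impacts are planned. The article does not say that this is the reason for the narrower list, and the perspective would not explain different wording for the two periods. Varying cost inputs also does not add a model state. A condensed article may leave an itemised costing list to a fuller plan, but it does state the model states and the outcomes.

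**Conclusion.** The point holds in three limited parts. First, the lifetime model as stated has no state for permanent residential care, an event the article itself treats as central; the direction of the resulting ICER error is unknown. Second, the community-living half of research question 2 has no outcome and cannot be answered from the measures listed. Third, the cost scope is inconsistent between the abstract, Primary outcome measures and Economic evaluation.

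The article supports no estimate of the actual error. Under the assumed inputs, AUS$500 of uncounted community cost per participant can carry the ICER across AUS$64,000 when the QALY gain is 0.02, while even AUS$2,000 does not when the gain is 0.05 (both with a counted incremental cost of AUS$1,000). The residential-care illustration spans AUS$8,000 in either direction and rests wholly on assumed annual costs and changes in time.

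**What to change.** - **Outcome.** Record for each participant the date of permanent residential-care entry and the date of death. Report time living in the community as the secondary outcome for the second half of research question 2. Because Trial status puts the study at 6 months post baseline in November 2018, state openly that this outcome was added during the trial.
- **Model.** Add permanent residential care as a Markov state with its own cost and utility. Given few transitions, a sensitivity analysis is the minimum. If the state stays out of the base case, say why and say how placed participants are handled.
- **Costs.** Reconcile the abstract, Primary outcome measures and Economic evaluation. Cost the same categories in both periods (hospital, GP, allied health, nursing and support services from the existing form), within the stated perspective. Name a price source suitable for community services, and state which items the perspective excludes.

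The cost is two date fields and revised analysis wording, since service use is already on the form. The downsides are sparse transitions in about 120 participants followed to 9 months, hence imprecise transition probabilities, and an ICER that may become less favourable.
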